### Statistical analyses

#### Primary analyses

Baseline socio-demographic and clinical characteristics of the MBCT group and the TAU group will be compared to check whether these characteristics will have been evenly distributed by randomisation. The primary analyses will be aimed at comparing results on the outcome measures at three months after baseline between the MBCT group and the TAU group, controlling for baseline levels and possible other baseline differences between intervention and control groups (despite randomisation).

The outcome data will be analysed and reported according to the CONSORT guidelines and will include both intention-to-treat analyses and per-protocol analyses with the treatment-adherent sample (patients in the MBCT group have to attend at least four of MBCT sessions and patients in the TAU group do not attend a mindfulness-based programme). Percentages of improved, recovered, unchanged and worsened patients in the intervention and control groups will be provided on the basis of predefined cut-off scores (*T-*score greater than 65) and standard deviations. In addition, a Cohen’s *d*-type effect size will be calculated.

In order to investigate consolidation of treatment effect at 6 and 9 months after baseline, we will study whether there is an intervention by time interaction with a mixed model to accommodate for repeated measures. Such an interaction would imply that long term effects are different from short term effects. In addition, regression models will be used to derive prediction models for therapy outcome.

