### Participants

The study population will consist of adults with ADHD. To enhance generalisability, the study is conducted in three different mental health centres for patients with ADHD in the south-east of the Netherlands: the Department of Psychiatry of the Radboudumc in Nijmegen, the Reinier van Arkel Group in the Jeroen Bosch hospital in ‘s Hertogenbosch and Dimence in Deventer. Each centre has a specialized outpatient clinic for adults with developmental disorders, like ADHD.

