### Randomisation

Randomisation will be computerised and be stratified for centre. Block randomisation with varying predefined block sizes is used combined with minimisation. Block randomisation will be dominant over minimisation. The randomisation will be minimised taking account of: a) use of medication for ADHD (medication versus no medication); b) past participation in a psycho-education training (psycho-education versus no psycho-education); c) gender (male versus female); and d) subtype ADHD (combined, hyperactive-impulsive, inattentive and not otherwise specified). The researcher will be blind for the block sizes.

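### The primary model adjusts for whatever baseline differences turn up between arms, with no list or criterion, and this rule tends to pass over the stratification and minimisation factors

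*Protocol article*

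**What the plan says.** In the protocol article, the Primary analyses section first states that baseline socio-demographic and clinical characteristics of the two arms "will be compared to check whether these characteristics will have been evenly distributed by randomisation". The primary three-month comparison is then made "controlling for baseline levels and possible other baseline differences between intervention and control groups (despite randomisation". The section lists no candidate characteristics and does not say what counts as a difference: a p-value, a standardised difference or judgement.

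The Randomisation section uses five factors for allocation:
- Centre: "Randomisation will be computerised and be stratified for centre". There are three centres (Participants section).
- ADHD medication: "The randomisation will be minimised taking account of: a) use of medication for ADHD (medication versus no medication".
- Psycho-education: "past participation in a psycho-education training (psycho-education versus no psycho-education".
- Gender: "gender (male versus female".
- Subtype, in four levels: "subtype ADHD (combined, hyperactive-impulsive, inattentive and not otherwise specified".

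The same section gives the blocks priority over minimisation. None of the five factors is named as a model term in the Primary analyses section. The Sample size section assumes an ANCOVA whose only stated covariate information is a pre-post correlation of 0.5.

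**The concern.** Under proper randomisation, a baseline difference between arms arises by chance. Its size says nothing about whether the variable predicts outcome, and predicting outcome is the reason to adjust. A rule that admits covariates because they differ therefore selects on the wrong property, after the data have been seen by arm. Without a list or criterion, two analysts who both follow the text can fit different primary models and report different primary p-values.

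The rule also pulls against the allocation scheme. Factors that allocation tries to balance are the least likely to show a difference, so they tend to stay out of the model. When such factors are prognostic, an analysis that ignores them reports a standard error larger than the allocation warrants. The test becomes conservative and some power is lost.

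**Working it through.** **1. The plan's own figure.** Inputs from the Sample size section: difference 4, SD 7.5, correlation 0.5, two-sided alpha 0.05, power 80 %, drop-out 25 %.
- Residual SD = 7.5 × √(1 − 0.5²) = 6.495.
- n per arm = 2 × [6.495 × (1.960 + 0.842) / 4]² = 41.4, so 42 (normal approximation) or 43 (t distribution). The plan says about 45.
- 45 / 0.75 = 60 per arm, 120 in total.

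The figure is reproduced closely enough. It rests on baseline adjustment alone and does not depend on the covariates at issue.

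**2. Cost of adding the allocation factors.** Degrees of freedom: centre 2, medication 1, psycho-education 1, gender 1, subtype 3, total 8. With 90 evaluable patients the residual degrees of freedom fall from 87 to 79. If the factors have no prognostic value and are balanced, power falls from 82.4 % to 82.3 %.

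**3. Effect of leaving them out.** Let R² be the share of residual variance (after baseline) that the factors explain. The documents give no value, so 5, 10 and 20 % are assumed. With full balance:
- Reported SE / true SE = 1/√(1 − R²).
- The effective critical value is 1.988/√(1 − R²) (t, 87 df), which gives the type I error.
- The SE without the factors is 6.495 × √(2/45) = 1.369. The true SE is 1.369 × √(1 − R²), and power follows from the noncentral t.

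| Assumed R² | Reported/true SE | Type I error, factors omitted | Power, omitted | Power, included (79 df) |
|---|---|---|---|---|
| 5 % | 1.026 | 4.4 % | 83.0 % | 84.1 % |
| 10 % | 1.054 | 3.9 % | 83.6 % | 86.0 % |
| 20 % | 1.118 | 2.9 % | 85.0 % | 89.7 % |

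Full balance makes these upper bounds on the effect.

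**4. Chance flags.** If a difference meant p<0.05 and the characteristics were independent (both assumptions), the chance of at least one flag by luck is 1 − 0.95^10 = 40 % for 10 characteristics and 1 − 0.95^15 = 54 % for 15.

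**5. Simulation of the rule.** Setup: 90 patients, minimisation on four binary factors, ten other characteristics. The factors and the other characteristics each explain an assumed 5/10/20 % of residual variance. There were 6,000 null runs and 3,000 runs at a difference of 4 per setting. Only the ten other characteristics were candidates for selection.

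| Model | Type I error (5/10/20 %) | Power (5/10/20 %) |
|---|---|---|
| Baseline only | 4.8 / 3.8 / 3.1 % | 83.7 / 81.8 / 83.6 % |
| Baseline plus characteristics with p<0.05 | 4.6 / 4.0 / 2.5 % | 81.9 / 81.5 / 83.2 % |
| Baseline plus allocation factors | 5.2 / 4.7 / 4.9 % | 84.2 / 84.5 / 89.6 % |
| Smallest p over no selection and thresholds 0.05, 0.1, 0.2 | 6.2 / 5.2 / 4.2 % | not a valid test |

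One fixed threshold does not inflate type I error. Free choice among thresholds raises it relative to a fixed threshold, and in the first setting takes it above 5 %.

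**The case against.** The strongest case on the other side has four parts.

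- **The omission is an absence in a condensed article.** The text does not exclude the allocation factors, and an analysis plan that is not shown could include them. This stands. A reader might infer that the trial will certainly analyse without them, and the document does not support that. It does not dispose of the selection rule, which is stated outright: a plan that fixed the covariates in advance would have to depart from that sentence.
- **Balance is not guaranteed.** Blocks take priority over minimisation, and the 25 % drop-out allowed for can disturb balance among evaluable patients. This also stands. It would be tempting to say that the factors will show no imbalance and are sure to be left out, but the text supports only a tendency.
- **The size rests on assumed inputs.** The document states no test, threshold, number of characteristics or R². That is correct; the figures above are illustrations over a range.
- **The harm is limited.** A reader might infer a biased estimate, an inflated error rate or an underpowered trial. None follows. Omitting balanced factors leaves the estimate unbiased and the test conservative, and power stays above the planned 80 % in every case examined. What remains is analyst discretion and power given away.

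**Conclusion.** The point holds in this form. The stated rule lets the primary model depend on chance imbalance seen by arm, with no list or criterion, and it tends to pass over the factors used in allocation. The consequences are an unfixed primary model, a somewhat conservative test and a power loss of about 1 to 5 percentage points, if the factors explain 5 to 20 % of residual variance and are fully balanced. Under free choice of threshold, simulated type I error reached 6.2 % at most. The estimate is not biased and the sample size is unaffected. Confidence is high on the selection rule, which is explicit, and lower on the omission, which an unseen analysis plan could repair. Severity is moderate: this is a free improvement, not a flaw that invalidates the primary analysis.

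**What to change.** Remove the clause on other baseline differences and fix the primary model before any data are seen by arm: an ANCOVA of three-month CAARS-INV on arm, baseline CAARS-INV, centre, ADHD medication, past psycho-education, gender and ADHD subtype. State a rule for sparse subtypes in advance; for example, any subtype with fewer than a pre-stated number of patients, counted blind to arm, is merged with the next smallest. Describe baseline characteristics by arm without tests that drive the model. Keep adjustment for other observed imbalances as a sensitivity analysis only.

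The cost is a few sentences of analysis text. The five factors are already needed to randomise each patient, so no new data are collected. The model uses 8 more degrees of freedom out of 87, which costs about 0.1 percentage point of power if the factors are balanced but turn out not to be prognostic; residual imbalance would add a little. N = 120 stays as planned.

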### Sample size

The power calculation has been based on our previous randomised controlled study consisting of 103 adults with ADHD (Hepark et al., submitted) in which we demonstrated a significant difference in post-assessment clinician-rated ADHD symptoms (CAARS-INV) [36] between the MBCT and waitlist control group. Based on these study results, we expect a post-treatment difference of 4 between the two groups with a standard deviation of 7.5. Using a two-sided test with an alpha of 0.05, a power of 80 % and analyzing the data using ANCOVA assuming the correlation between pre- and post-assessments to be 0.5, we would need approximately 45 patients per arm. Taking account for loss of power due to drop out of 25 %, we intend to include 120 patients, 60 patients per group.

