## Discussion

Adult ADHD has a substantial personal and economic impact and consequently there is a high need for evidence-based treatments for this patient group. Although pharmacotherapy has shown to be effective in reducing ADHD symptoms and its economic impact, there is a call for psychosocial interventions to offer in addition to pharmacotherapy or as an alternative treatment. At this moment research examining the effectiveness of psychosocial interventions for adult ADHD is still in its infancy. Mindfulness training, such as MBCT, is a promising psychosocial intervention, which can be offered in a group format. Considered from an economic perspective, this is an advantage over treatment on individual basis. Previous studies support the feasibility of mindfulness training for this patient group and provide preliminary, but consistent evidence that this intervention reduces ADHD symptoms and improves executive functioning. However, the methodology of these studies is limited by single-centre enrolment [27–29], and (Hepark et al., submitted) lack of follow-up periods [27–29], and (Hepark et al., submitted) small sample sizes [27–29], lack of a control group [27, 28] and lack of blinded assessments [27–29]. Our study will take account of these limitations and will examine the effectiveness of MBCT in adults with ADHD in further detail.

To our knowledge, this is the first properly powered randomised controlled study in this field, that contains blinded outcome assessments and an intention-to-treat analysis. Besides, a follow-up period with a length of six months after the end of treatment is included to consider potential long-term effects of MBCT. To enhance generalisability, this study is conducted in three different mental health centres with expertise in treating adults with ADHD. Additionally, cost-effectiveness will be assessed to evaluate whether MBCT is a cost-effective intervention compared to the treatment as usual and to examine the financial consequences of implementing this intervention. This trial will offer valuable information on whether MBCT has an effect on clinician-rated and self-reported ADHD symptoms, executive functioning, general functioning, positive mental health, self-compassion and medical and societal costs in comparison to treatment as usual.

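### Lasting effect at 6 and 9 months is examined only through an intervention-by-time interaction, which cannot show that MBCT still beats TAU and has low power to detect a halved effect

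*Protocol article*

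**What the plan says.** In the protocol article, Statistical analyses (Primary analyses), the primary comparison is between arms at 3 months, adjusted for baseline. For persistence of the effect at 6 and 9 months the article says "we will study whether there is an intervention by time interaction with a mixed model to accommodate for repeated measures", and it explains a positive finding: "Such an interaction would imply that long term effects are different from short term effects". It mentions no between-arm estimate at 6 or 9 months, and it does not say what a negative finding would mean.

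The Sample size section covers the post-treatment comparison only: "we expect a post-treatment difference of 4 between the two groups with a standard deviation of 7.5", "assuming the correlation between pre- and post-assessments to be 0.5", leading to "we would need approximately 45 patients per arm" and, after 25% dropout, 60 per arm.

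The Discussion presents the follow-up as a strength: "a follow-up period with a length of six months after the end of treatment is included to consider potential long-term effects". Under Procedure and treatment allocation, TAU patients are offered MBCT only once the 9-month assessment is complete, so a randomised comparison is available at both later visits.

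**The concern.** The clinical question is whether MBCT plus TAU is still better than TAU at 6 and 9 months, and by how much. The interaction asks something else: whether the arm difference changes between visits. Neither of its outcomes answers the clinical question.

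- A significant interaction fits an effect that has faded and also one that has grown.
- A non-significant interaction fits a maintained effect, a partly lost effect that the test missed, and no effect at any visit.

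Support for persistence could therefore come only from failing to reject, in a trial that was not sized for this contrast. Long-term follow-up is one of the advances the article claims over earlier studies, so the statement on lasting benefit needs a firmer basis.

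**Working it through.** **Inputs from the Sample size section.** Difference 4, SD 7.5, baseline-to-post correlation 0.5, two-sided alpha 0.05, power 80%, about 45 per arm after dropout, 60 per arm randomised.

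**Assumptions.** The article gives no correlation ρ between follow-up visits. I take 0.5 (its baseline-to-post value) to 0.7 and vary it further below. SD is 7.5 at every visit. Baseline correlates equally with each follow-up visit, so baseline adjustment does not alter the SD of the change between visits.

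**Reproducing the stated size.** The ANCOVA residual SD is 7.5 × √(1 − 0.5²) = 6.50. Then n per arm = 2 × (6.50 × (1.960 + 0.842) / 4)² = 41.4, so 42, or 43 with the t distribution. This is close to the stated 45. Power at 45 is 82–83%, and 45 / (1 − 0.25) = 60. The sizing for the primary comparison is sound.

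**Power of the interaction, 3 versus 9 months.**

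- SD of within-patient change = 7.5 × √(2(1 − ρ))
- SE of the change in effect = SD of change × √(2/n)
- Power ≈ Φ(δ/SE − 1.96), where δ is the change in the arm difference

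| n per arm | ρ | SD of change | SE | Power, 4 falls to 2 | Power, 4 falls to 0 |
|---|---|---|---|---|---|
| 45 | 0.5 | 7.50 | 1.58 | 24% | 72% |
| 45 | 0.7 | 5.81 | 1.22 | 37% | 90% |
| 60 | 0.5 | 7.50 | 1.37 | 31% | 83% |
| 60 | 0.7 | 5.81 | 1.06 | 47% | 96% |

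For example, at 45 per arm and ρ = 0.5, 2/1.58 − 1.96 = −0.70, which gives 24%. Noncentral-t values are at most about one percentage point lower. At 45 per arm a halving is missed 63–76% of the time.

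**Sensitivity.**

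- A 2-df test over the 3-, 6- and 9-month visits (compound symmetry, 45 per arm, ρ 0.5 to 0.7) has 24–37% power for effects of 4, 2, 2 and 19–29% for 4, 3, 2.
- At ρ = 0.8, power for a halving is 51–52% with 45 per arm and 63–64% with 60.
- Power of 80% for a halving needs ρ of about 0.9 with 45 per arm or 0.87 with 60. Otherwise it needs about 221 per arm at ρ = 0.5 or 133 at ρ = 0.7.
- At 45 per arm and ρ = 0.5, the smallest change detectable with 80% power is 2.80 × 1.58 = 4.4 points, more than the whole expected effect.

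**Direct arm difference at 9 months, baseline-adjusted.** With the baseline correlation of 0.5 carried to month 9, SE = 6.50 × √(2/45) = 1.37 and the 95% CI half-width is 1.96 × 1.37 = 2.7 points (2.3 with 60 per arm). At 45 per arm, power is about 82% if 4 points persist and about 30% if 2 points remain.

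**The case against.** A reader might infer that the plan commits itself to reading a non-significant interaction as a lasting effect. The text does not support that. It explains only what a significant interaction would mean, and that direction is valid. What stands against the plan is narrower: no other analysis is named for the question, and this one cannot give a positive answer to it.

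A reader might also fear that baseline enters the model as one of the repeated measures, so that the interaction would test the short-term effect itself. The sentence contrasting long-term with short-term effects points to the post-baseline visits, so this is not part of the point.

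It is also tempting to set the interaction's 24% against the direct contrast's 82%. Those figures refer to different targets. For 2 points the two have 24–37% and about 30%; for 4 points, 72–90% and 82%. The direct contrast is not generally more sensitive. With a true remaining effect of 2, its interval would run on average from about −0.7 to 4.7, which excludes neither no effect nor a full 4 points.

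Two further objections carry weight. A mixed model uses partial follow-up, so 45 per arm is a cautious figure; but 60 per arm still gives only 31–47% for a halving. And a journal article may leave visit-specific contrasts to a full analysis plan, while low power on a secondary question is not in itself an error. That would dispose of a complaint about missing detail. It does not dispose of the fact that the article chooses a tool for this question, and that tool answers a different one.

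**Conclusion.** The point holds as a weakness in how the long-term question is to be answered. The interaction cannot show whether MBCT still beats TAU at 6 or 9 months, and its non-significance would not show maintenance. Under the article's own effect and SD, and a follow-up correlation of 0.5 to 0.7, it would detect a halved effect in roughly a quarter to a third of trials with 45 per arm (24–37%), and in fewer than half with 60 (31–47%). Detection of complete loss is moderate to good (72–90% at 45 per arm). These figures rest on the assumed correlation and a constant SD; power for a halving reaches 80% only at a correlation of about 0.87 to 0.9. The 3-month primary comparison and its sample size are not affected.

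**What to change.** Keep the mixed model over the 3-, 6- and 9-month visits, with baseline CAARS-INV as covariate, and add to the analysis text:

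- The MBCT–TAU difference with 95% CI will be reported at 6 and at 9 months, and the statement on long-term benefit will rest on these estimates.
- The change in effect from 3 to 9 months will be reported as an estimate with 95% CI (half-width about 1.96 × 1.58 = 3.1 points at a correlation of 0.5, or 2.4 at 0.7, with 45 per arm).
- A non-significant interaction will not be taken to show that the effect is maintained.

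The cost is a few sentences, with the same model, data and patients. The 3-month primary ANCOVA need not change. The gain is not power, which stays at about 30% for a 2-point effect at 9 months with 45 per arm. It is a direct answer to whether MBCT is still better than TAU, with its uncertainty in view.

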#### Secondary analyses

##### Cost-effectiveness analysis

For each patient in the MBCT and TAU group: a) costs; b) treatment response; and c) QALYs will be collected over the study period of nine months. Total costs for each patient will be obtained by multiplying the resource use as measured with the TiC-P with standard costs, based on the Dutch guideline for costing research [53]. Overall mean and median costs will be compared across the two groups and where relevant, differences will be calculated inclusive of 95 % confidence intervals. Treatment response will be based on our primary outcome, the investigator-rated version of the CAARS. QALYs will be assessed by the SF-12. At baseline and each follow-up interval, each patient is assigned a utility score based on the SF-12. From these utility scores QALYs will be calculated for each patient using the Area Under the Curve (AUC) method. Mean and median QALYs will be compared across the two groups and where relevant, differences are calculated inclusive of 95 % confidence intervals.

If MBCT is more costly and more effective than TAU, an incremental cost-effectiveness ratio (ICER) will be calculated by dividing the extra costs by the extra effects. ICERs are computed to obtain the costs per responder and the costs per QALY gained. This will give an estimation of the extra costs that are needed to gain one responder or QALY. If this is below the societal willingness to pay, mindfulness training is deemed cost-effective. If one comparator is less costly and more effective, it dominates the other and no ICER is necessary to determine cost-effectiveness. If MBCT is less effective and less costly, ICERs will be calculated representing the savings per QALY lost. Uncertainty surrounding the costs, effects and ICER will be addressed by means of bootstrapping.

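### The economic analysis names no baseline covariate for QALYs or costs, so chance imbalance stays partly in the QALY difference and precision is lost

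*Protocol article*

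**What the plan says.** The Cost-effectiveness analysis section sets out the following sequence.

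- Utilities: "At baseline and each follow-up interval, each patient is assigned a utility score based on the SF-12". They are turned into QALYs by area under the curve over nine months.
- QALY comparison: "Mean and median QALYs will be compared across the two groups and where relevant, differences are calculated", with 95% confidence intervals.
- Cost comparison: "Overall mean and median costs will be compared across the two groups", again with 95% intervals for differences.
- Uncertainty: "Uncertainty surrounding the costs, effects and ICER will be addressed by means of bootstrapping".

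No covariate appears in any of these steps. The section on Primary analyses does adjust for the baseline value of the outcome and for other baseline imbalances, but ties that to the comparison at three months.

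The data needed for adjustment are collected. Utilities are scored at baseline. The TiC-P is a self-report instrument, and Procedure and treatment allocation has self-report questionnaires completed at all four time points. Under Randomisation, allocation is stratified by centre and minimised on medication use, psycho-education, gender and ADHD subtype. Neither utility nor prior cost is balanced by design.

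**The concern.** A QALY computed by area under the curve contains the baseline utility as one of its terms, and the later utilities are correlated with it. When group means are compared without that covariate, any difference in baseline utility that arises by chance stays partly in the estimated QALY gain. The variation between patients that baseline utility could explain stays in the standard error. The same precision argument applies to costs, although total follow-up cost does not contain baseline cost.

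The QALY difference is the denominator of the cost-effectiveness ratio, and the article's decision rule depends on which arm is more effective and which is more costly. Avoidable noise in the incremental QALY therefore matters to the economic conclusion. The trial was sized on CAARS-INV, with about 45 evaluable patients per arm, and not on QALYs.

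**Working it through.** **1. The plan's own figures.** The only power figures are for CAARS-INV: "we expect a post-treatment difference of 4 between the two groups with a standard deviation of 7.5", 80% power, two-sided alpha 0.05, and "assuming the correlation between pre- and post-assessments to be 0.5".

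- Normal approximation: n = 2 × (7.5 × (1.960 + 0.842) / 4)² × (1 − 0.5²) = 55.2 × 0.75 = 41.4, so 42 per arm.
- t-based versions give 43 or 44, close to the stated figure ("we would need approximately 45 patients per arm").
- Dropout: 45 / 0.75 = 60 per arm, as stated.

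The article gives no standard deviation, correlation or precision for QALYs or costs. Its 0.5 is a pre-post correlation for CAARS-INV. The range of 45 to 60 per arm carries forward; the utility and cost correlations below are assumptions.

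**2. Weight of baseline in the QALY.** Visits fall at 0, 0.25, 0.50 and 0.75 year. Trapezoid weights w are 0.125, 0.25, 0.25 and 0.125 year, summing to 0.75. Baseline holds 0.125 / 0.75 = 1/6 of the weight.

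**3. Expected carry-over of a baseline difference.** With equal variances at all visits, the slope of QALY on baseline utility is Σ wⱼ × corr(u₀, uⱼ).

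- Equal correlation 0.5: 0.125 + 0.5 × 0.625 = 0.4375.
- AR(1) decay, adjacent-visit correlation 0.5: 0.125 + 0.25 × 0.5 + 0.25 × 0.25 + 0.125 × 0.125 = 0.328.

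**4. Precision.** R² = slope² / (w′Rw), where R is the correlation matrix. Adjustment multiplies the standard error by √(1 − R²).

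- Equal correlation 0.5: Σw² = 0.15625, so w′Rw = 0.15625 + 0.5 × (0.5625 − 0.15625) = 0.3594. R² = 0.1914 / 0.3594 = 0.533, and √(1 − 0.533) = 0.68, so the interval is about 32% narrower.
- AR(1) 0.5: w′Rw = 0.3164. R² = 0.1077 / 0.3164 = 0.340, and √(1 − 0.340) = 0.81, so the interval is about 19% narrower.

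**5. Costs.** Take the sum of three follow-up periods, with one baseline period as covariate and equal variances. At equal correlation 0.5, R² = 1.5² / 6 = 0.375. Under AR(1) 0.5, R² = 0.875² / 5.5 = 0.139.

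**6. Range.**

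| Correlation | Structure | QALY variance cut | QALY interval narrower | Cost variance cut | Cost interval narrower |
|---|---|---|---|---|---|
| 0.3 | equal | 35% | 19% | 17% | 9% |
| 0.3 | AR(1) | 21% | 11% | 4% | 2% |
| 0.5 | equal | 53% | 32% | 37.5% | 21% |
| 0.5 | AR(1) | 34% | 19% | 14% | 7% |
| 0.8 | equal | 81% | 57% | 74% | 49% |
| 0.8 | AR(1) | 67% | 42% | 51% | 30% |

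**7. Size of an ordinary chance imbalance.** Assume a utility SD of 0.12, equal correlation 0.5 and 60 per arm. One standard error of the baseline difference is 0.12 × √(2/60) = 0.0219. Its expected effect on the QALY difference is 0.4375 × 0.0219 = 0.0096. For SDs of 0.10 to 0.15 and 45 to 60 per arm, the effect runs from about 0.008 to 0.014. For scale, an assumed utility gain of 0.03 held from month 3 to month 9 is worth 0.03 × 0.625 = 0.019 QALY.

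**The case against.** The strongest objection is that the absence of adjustment is inferred. The article never calls the comparison unadjusted, a comparison of means with a confidence interval could be made by regression, and a fuller protocol or economic analysis plan, not shown here, may name covariates. The possibility stands. It does not dispose of the point, because this section is specific about method: it fixes the QALY construction, the statistics compared, the intervals, the ratio rules and the bootstrap. The one explicit statement of baseline control sits elsewhere and is limited to three months.

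It is also fair to say that randomisation makes the difference in means unbiased. That stands in full: the issue is chance imbalance and efficiency, not systematic error.

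A reader might infer more than the documents support:

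- **Half the precision is lost, for QALYs and costs alike.** About half is a variance figure for QALYs under one assumed correlation structure. On the interval scale the corresponding figure is about a third, and for costs the gain is generally smaller.
- **An ordinary imbalance would erase the QALY gain or reverse the verdict.** Under the assumptions in step 7, one standard error takes away about half of the assumed gain (0.0096 of 0.019). Erasing it needs about 1.96 standard errors in the unfavourable direction, roughly a 2.5% chance at 60 per arm (about 1.7 standard errors, 4.5%, at 45). The article states no cost difference or willingness-to-pay value, so no reversal can be calculated.
- **A bootstrap interval for the ratio is planned.** The text says only that uncertainty will be addressed by bootstrapping, which is compatible with a cost-effectiveness plane or acceptability curve.
- **Medians drive the decision.** They are reported, but the decision rule uses extra costs, extra effects, dominance and willingness to pay.

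**Conclusion.** The point holds as a choice of analysis that should be improved. As written, the nine-month economic comparison uses group means of QALYs and costs with no baseline covariate, although the QALY includes baseline utility and the trial collects both baseline measures. The estimate remains unbiased on average.

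The cost is a partial carry-over of chance imbalance and a wider QALY interval than necessary. The direction is the same across all the correlations examined, but the size is uncertain because it depends on utility and cost correlations that the article does not give, on equal variances across visits, and on the correlation pattern. The case for adjusting QALYs is stronger than the case for adjusting costs. Because only the condensed article is available, the finding concerns its stated method and does not show that adjustment was ruled out.

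**What to change.** Amend the Cost-effectiveness analysis section to say that:

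- incremental QALYs are estimated by regression on arm and baseline SF-12 utility, with centre included as the stratification factor;
- incremental costs are estimated by regression on arm and baseline TiC-P cost, with centre included;
- both regressions are refitted within each bootstrap replicate, on the same resampled patients, so that the uncertainty in costs, effects and their ratio reflects the adjusted estimates.

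Unadjusted means and medians can stay as description. If a fuller plan already specifies this, a sentence in the section saying so is enough. The change needs no new data, visits or patients, only analysis code.
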